## Abstract

**Background:**

There are a variety of treatment options for Bell's palsy. Evidence from randomized controlled trials indicates corticosteroids can be used as a proven therapy for Bell's palsy. Acupuncture is one of the most commonly used methods to treat Bell's palsy in China. Recent studies suggest that staging treatment is more suitable for Bell's palsy, according to different path-stages of this disease. The aim of this study is to compare the effects of prednisolone and staging acupuncture in the recovery of the affected facial nerve, and to verify whether prednisolone in combination with staging acupuncture is more effective than prednisolone alone for Bell's palsy in a large number of patients.

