### Patients and enrolment

A power analysis is undertaken to calculate before conducting this trial: α = 0.05 and power = 80%. According to the previous literature, 70% of patients recover completely without treatment (placebo) compared with 80% of patients treated with prednisolone, acupuncture, or both. This difference of 10% is regarded as a clinically significant improvement. Therefore, the sample size in this trial can be estimated initially according to PASS software. Each group needs at least 172 patients (assuming a 15% dropout rate), 1200 patients in six groups will be enrolled in the study.

Baseline assessments before the start of treatment include neurological examination, grading of facial function, measurement of ipsilateral pain, documentation of concurrent medication. Patients with acute, unilateral, peripheral facial palsy, who are referred from neurology, internal medicine or emergency departments, or who seek care directly, are screened by physicians in 16 public county hospitals and Xijing hospital in Shaanxi province. There is at least one experienced neurology physician, who is responsible for implementing the study, with a special interest in facial palsy in each hospital. A written consent form will be obtained from each patient and retained by the investigators.

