### Statistics

The study will be performed using intention to treat. In this analysis, all randomized patients will receive at least one therapy, but patients who did not start treatment will be excluded (modified intention-to-treat analysis). The last-observation-carried-forward method will be used for the modified intention-to-treat analysis. The missing data points will be imputed in the post-baseline follow-up visits from the last observation available for each patient. An interaction test was done to show the synergistic effect of the combination of prednisolone and acupuncture. Categorical variables will be compared by using Fisher's exact test. Cox proportional hazards models will be used to estimate the hazard ratio (HR) of recovery, including 95% CI. These will be compared between groups by using t-test, and Mann-Whitney, or Chi-squared tests as appropriate. All statistical assessments are two-sided, and a P value < 0.05 is considered statistically significant.

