## Discussion

Bell's palsy is a common disease. Recent evidence from large randomized controlled trials indicates that corticosteroids are associated with a reduced risk of un-satisfactory recovery in Bell's palsy. Acupuncture, a therapy of Chinese traditional medicine, has been recognized as an alternative treatment method for many diseases. Its effectiveness for Bell's palsy has been shown by a few clinical trials in recent years [7-10]. However, the best intervention time for acupuncture has been uncertain to date. Many studies testified the effectiveness of staging acupuncture by comparing results with non-staging acupuncture [14-18]. Although some research results showed that there were differences between staging acupuncture and non-staging acupuncture to treat Bell's palsy, these trials had some methodological defects. For instance, four clinical controlled trials illustrated that the therapeutic effect of acupuncture treatment at different path-stages was better than that of routine acupuncture treatment for treating facial paralysis [16-19]. Randomization method was not used in these trials, and the sample size was smaller than 80 clinical cases in two studies [16,17], the biggest one being less than 130 clinical cases [18,19]. In addition, the side effects during acupuncture treatment and the follow-up tests were not reported in any of these trials. The design of the control group was illogical as well [20]. So which method is the best treatment at different path-stages for Bell's palsy needs to be investigated. Staging acupuncture, when administered with corticosteroids, may also be associated with additional benefits. In summary, the purpose of this trial is to provide evidence of the effectiveness of staging acupuncture to treat Bell's palsy, and to find out the best approach for treating this disease.

We expect to complete recruitment by December 2011 and anticipate that the results from this study will have implications for health care resourcing and will facilitate improvements in the treatment of people with Bell's palsy. The results of this study will also allow us to determine, for the very first time, if a prednisolone intervention alone is as effective at facilitating facial nerve recovery as an intervention involving both prednisolone and staging acupuncture. These results may have important implications for the design of sustainable cost-effective health services for people with Bell's palsy.

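### The plan names no acute-versus-resting contrast across both drug levels, and its 172 per group with 80% power fits only comparisons with two groups pooled on each side

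*Protocol article*

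**What the plan says.** All references are to the Protocol article. The Abstract and the Interventions section list six arms, numbered here as in the Abstract: 1 placebo, 2 prednisolone, 3 placebo with acute-stage acupuncture, 4 prednisolone with acute-stage acupuncture, 5 placebo with resting-stage acupuncture, 6 prednisolone with resting-stage acupuncture. This is a 2 x 3 layout.

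Patients and enrolment sets "α = 0.05 and power = 80" percent and assumes that "70% of patients recover completely without treatment (placebo) compared with 80% of patients treated with prednisolone, acupuncture, or both". It adds: "This difference of 10% is regarded as a clinically significant improvement". The result is given per group: "Each group needs at least 172 patients (assuming a 15% dropout rate), 1200 patients in six groups will be enrolled in the study". The section does not say whether the two sides being compared are single groups or pooled groups.

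Statistics plans Cox models, Fisher's exact test and a test of the prednisolone-by-acupuncture interaction. On comparisons it says "These will be compared between groups by using t-test, and Mann-Whitney, or Chi-squared tests as appropriate". The criterion is "All statistical assessments are two-sided, and a P value < 0.05 is considered statistically significant".

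Two questions motivate the acupuncture arms. On timing, the Discussion says "However, the best intervention time for acupuncture has been uncertain to date". On add-on benefit, the Abstract aims to "verify whether prednisolone in combination with staging acupuncture is more effective than prednisolone alone".

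**The concern.** The acute-versus-resting question occurs twice in this layout: 3 v 5 under placebo and 4 v 6 under prednisolone. A plan that speaks of size per group and of tests between groups invites the analyst to answer it with two separate comparisons, each on half the relevant patients. The interaction test is the only stated use of the crossed structure, and it addresses synergy, not timing.

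Two things are at stake. The trial could miss a timing difference that its 1200 patients are able to show, or end with one significant and one non-significant pair for the same question and no stated rule on which counts. And a reader of the sample-size paragraph may believe that any two groups are compared with 80% power.

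**Working it through.** **Inputs.** From Patients and enrolment: 70% v 80%, alpha 0.05, power 80%, 15% dropout, 172 per group, 1200 in total. From Statistics: two-sided tests. Assumed: equal allocation, so 1200/6 = 200 per group, and 200 x 0.85 = 170 after loss.

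**1. The plan's own figure.** With the arcsine formula, n per side = 2[(1.960 + 0.842)/h]², where h = 2 arcsin√0.8 − 2 arcsin√0.7 = 0.2320. This gives 291.7, rounded up to 292.
- Inflated for dropout: 292/0.85 = 343.5, so 344 per side.
- Spread over two groups per side: 344/2 = 172, the stated figure.
- The pooled-variance formula gives 294, then 294/0.85 = 346 and 346/2 = 173.

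Read as one group against one group, the same inputs need 343 to 369 per group (two-sided variants, after dropout). One-sided variants need 270 to 296 and log-rank variants 231 to 296. None of these gives 172.

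**2. What 172 delivers.** Power = Φ[(0.10 − 1.960 s0)/s1], with s0 = √(2 x 0.75 x 0.25/n) and s1 = √((0.7 x 0.3 + 0.8 x 0.2)/n). With 172 x 0.85 = 146 evaluable per group:
- two groups pooled per side, 292 v 292: s0 = 0.0358, s1 = 0.0356, power 79.8%;
- single groups, 146 v 146: s0 = 0.0507, s1 = 0.0503, power 50.5%.

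If 172 is instead the number left after dropout, single groups have 57.3% and pooled pairs (344 v 344) 85.9%.

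**3. The timing question with 1200 enrolled.** The assumed difference is 10 points, 70% v 80%. For the contrast stratified by drug, power = Φ(d/SE − 1.960), where d is the mean of the two within-drug differences. With 170 per group and the same effect in both strata, d = 0.10 and SE = 0.0330, so d/SE = 3.03 and power is 85.8%.

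| | Single pair | 3+4 v 5+6, drug-stratified |
|---|---|---|
| After 15% loss (170 per group) | 56.8% | 85.8% |
| No loss (200 per group) | 63.8% | 90.8% |

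A stratified Mantel-Haenszel simulation (20,000 runs, 170 per group) gave 85.6%, and a rejection rate of 4.8% under no effect.

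**4. Other base rates, 170 per group, single pair v simple pooling (340 v 340).** 65% v 75%: 52% and 81%. 75% v 85%: 64% and 91%. 80% v 90%: 74% and 96%.

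**5. Where pooling loses, 170 per group.** The difference exists under one drug level only.
- 70% v 80% in one stratum, 80% v 80% in the other: d = 0.05, SE = 0.0319, power 35%, against 57% for the affected pair.
- 80% v 90% in one stratum, 80% v 80% in the other: d = 0.05, SE = 0.0290, power 41%, against 74% for the affected pair.

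**The case against.** A reader might infer that the trial was sized as six stand-alone groups. The plan's number speaks against that: stand-alone groups would need about 346 each, and 172 appears when two groups are pooled per side. A reader might also infer that the plan splits timing into two pairwise tests. It does not say so. No pairwise list is given, 3 v 5 and 4 v 6 are not mentioned, and Cox models with an interaction test fit a factorial analysis. Both inferences go too far.

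It can further be said that an article leaves contrasts and strata to the full protocol or SAP. That is largely fair, and the absence of a contrast list alone would be no finding. What remains is that the article gives a per-group size and an 80% power, and on the reconstruction found these hold only under pooling that it nowhere commits to.

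Three limits on the figures also stand:
- The 10-point timing difference is an assumption made here. The plan applies 10 points to treated v untreated and gives every treated group 80%, which implies no acute-resting difference.
- Deducting the full 15% is one end of a range. With last observation carried forward, many dropouts stay in the analysis.
- The powers are for proportions. If 70% v 80% is read as proportional hazards (hazard ratio about 1.34), log-rank power is about 64% for a single pair and 91% pooled after loss, 71% and 94% without. The levels shift but the gap remains.

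Finally, the trial looks for synergy and for a best combination, which need arm-level results. That is a reason to keep the separate pairs in the report, but not to leave out the stratified contrast.

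**Conclusion.** The point holds as a matter of specification and stated power. The plan names no contrast that uses all acupuncture patients for timing, and its 172 with 80% power matches only two pooled groups per side. Single-group comparisons at 70% v 80% have about 50% power at the stated minimum less 15%, 57% at 200 enrolled less 15%, and 64% at 200 without loss. One drug-stratified timing contrast on the same patients has about 86% and 91% in the last two cases, a gain of 27 to 29 points.

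This rests on equal allocation, an assumed 10-point timing difference, and a similar difference under placebo and prednisolone. The pooled basis of 172 is a reconstruction: it is the only one of the variants tried that fits, and the article does not confirm it. The documents do not support saying that the trial was designed or will be analysed as six separate groups. The change should be made, with medium confidence.

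**What to change.** In Statistics, name one acute-versus-resting hazard ratio (groups 3+4 v 5+6) from a Cox model stratified by prednisolone/placebo as the analysis of timing. Report 3 v 5, 4 v 6 and the planned interaction test beneath it.

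In Patients and enrolment, state that 172 and 80% apply to two pooled groups per side, once the trial team has confirmed that basis, and give the lower power of single-group comparisons next to it.

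A pooled add-on ratio (4+6 v 2) is optional and should not replace 4 v 2 and 6 v 2. It averages two needling techniques. At 80% v 90% with 170 per group it has 86% power against 74% for a single pair, but only 30% if just one stage works.

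The cost is wording and one stratified model, with no extra patients or data. The downside should be written into the plan: the pooled timing ratio is an average, with about 35-41% power if timing matters under one drug level only.

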## Discussion

Bell's palsy is a common disease. Recent evidence from large randomized controlled trials indicates that corticosteroids are associated with a reduced risk of un-satisfactory recovery in Bell's palsy. Acupuncture, a therapy of Chinese traditional medicine, has been recognized as an alternative treatment method for many diseases. Its effectiveness for Bell's palsy has been shown by a few clinical trials in recent years [7-10]. However, the best intervention time for acupuncture has been uncertain to date. Many studies testified the effectiveness of staging acupuncture by comparing results with non-staging acupuncture [14-18]. Although some research results showed that there were differences between staging acupuncture and non-staging acupuncture to treat Bell's palsy, these trials had some methodological defects. For instance, four clinical controlled trials illustrated that the therapeutic effect of acupuncture treatment at different path-stages was better than that of routine acupuncture treatment for treating facial paralysis [16-19]. Randomization method was not used in these trials, and the sample size was smaller than 80 clinical cases in two studies [16,17], the biggest one being less than 130 clinical cases [18,19]. In addition, the side effects during acupuncture treatment and the follow-up tests were not reported in any of these trials. The design of the control group was illogical as well [20]. So which method is the best treatment at different path-stages for Bell's palsy needs to be investigated. Staging acupuncture, when administered with corticosteroids, may also be associated with additional benefits. In summary, the purpose of this trial is to provide evidence of the effectiveness of staging acupuncture to treat Bell's palsy, and to find out the best approach for treating this disease.

We expect to complete recruitment by December 2011 and anticipate that the results from this study will have implications for health care resourcing and will facilitate improvements in the treatment of people with Bell's palsy. The results of this study will also allow us to determine, for the very first time, if a prednisolone intervention alone is as effective at facilitating facial nerve recovery as an intervention involving both prednisolone and staging acupuncture. These results may have important implications for the design of sustainable cost-effective health services for people with Bell's palsy.

Central randomization is used in our trial, which is a strict, complete randomization, and it ensures adequate concealment. During the whole trial, the patients are not aware of which group they are to be assigned to, but they do know they will receive acupuncture treatment at different path-stages. Additionally, this trial is a multicenter randomized controlled study, with six months' follow up, containing a large number of patients. Up to now, our trial is one of the largest randomized controlled trials addressing the effectiveness of prednisolone in combination with staging acupuncture treatment for Bell's palsy.

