## Background

Bell's palsy is an acute peripheral unilateral facial weakness or paralysis with an as yet unknown cause. Bell's palsy accounts for almost three quarters of peripheral facial palsies and the annual incidence is about 30 patients per 100 000. 71% of untreated patients with Bell's palsy will completely recover and 84% will have complete or near normal recovery. The remainder will have persistent moderate to severe weakness, facial contracture, or synkinesis [1-3]. Because of its unclear etiology, there has been longstanding controversy about what treatment should be given, with potential alternatives including corticosteroids, antiviral drugs, acupuncture and physiotherapy. Inflammation of the facial nerve is the most probable cause of Bell's palsy. Therefore corticosteroids are commonly used as treatment of Bell's palsy. A recent study shows significant short-term and long-term positive treatment effects of prednisolone in patients with Bell's palsy [4].

Acupuncture is a safe therapy with a low risk of adverse events in clinical practice [5]. It is one of the most commonly used treatments for Bell's palsy in China. Chinese traditional acupuncture is low cost and very convenient to local people. Though only limited experience has been reported with acupuncture for Bell's palsy [6], several studies provide increasing evidence for a beneficial effect of acupuncture as an adjunctive treatment of Bell's palsy [7-10]. Bell's palsy has different path-stages; it includes acute stage (1-7 days onset of disease), resting stage (8-20 days onset of disease) and restoration stage (21-90 days onset of disease) [11-14]. However, convincing evidence for the efficacy of staging acupuncture to treat Bell's palsy is lacking because of previous poor study designs, small sample sizes or unclear reporting treatment. It's not clear whether acupuncture is effective in different path-stages.

Thus, in view of these data, we designed this randomized controlled multicentre study of Bell's palsy patients, with the aim of comparing the effects of prednisolone and staging acupuncture in the recovery of the affected facial nerve. We also hoped to verify whether staging acupuncture along with prednisolone is more effective than prednisolone alone in larger number of patients, especially in terms of reducing their level of incapacity and improving their quality of life.

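### The Discussion promises to determine whether prednisolone alone is as effective as the combination, but the stated aim and tests address only superiority and no margin is given

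*Protocol article*

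**What the plan says.** The protocol article states one comparison, prednisolone alone against prednisolone plus staging acupuncture, in two ways.

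- **Abstract, Background:** the trial is to verify "whether prednisolone in combination with staging acupuncture is more effective than prednisolone alone".
- **Background, last paragraph:** the investigators hope to verify "whether staging acupuncture along with prednisolone is more effective than prednisolone alone".
- **Discussion:** the results will allow them to determine "if a prednisolone intervention alone is as effective at facilitating facial nerve recovery as an intervention involving both prednisolone and staging acupuncture". The next sentence links the results to the design of cost-effective services.

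The **Statistics** section gives one decision rule: "All statistical assessments are two-sided, and a P value < 0.05 is considered statistically significant". It names Fisher's exact, t, Mann-Whitney and chi-squared tests, an interaction test for synergy, and Cox models giving hazard ratios with 95% confidence intervals. It states no equivalence or non-inferiority hypothesis and no margin.

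The sizing in **Patients and enrolment** assumes that "70% of patients recover completely without treatment (placebo) compared with 80% of patients treated with prednisolone, acupuncture, or both", and adds: "This difference of 10% is regarded as a clinically significant improvement". That difference is between active treatment and placebo.

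**The concern.** Showing that one treatment is as effective as another requires excluding a difference large enough to matter, so that size has to be fixed beforehand. A test of difference does not do this: P above 0.05 says only that the data are compatible with no difference, and they may also be compatible with a worthwhile one.

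Two features of the text make this more than a quibble over a phrase. The Discussion speaks of determining the answer and draws a line from it to health-service design. The sizing paragraph gives the two regimens the same assumed recovery rate, so the plan itself makes a non-significant result for this contrast plausible. Such a result could then be presented as support for prednisolone alone while leaving open a clinically important benefit of adding acupuncture.

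**Working it through.** **1. The plan's own sample-size figure.** Patients and enrolment gives 172 per group (70% vs 80%, α = 0.05, power 80%, 15% dropout) and 1200 in six groups. The usual two-sided formula for a 1:1 comparison gives 294 per group, or 294/0.85 = 346 after dropout, so 172 is not reproduced. That is a separate matter. The check below uses the enrolled total and does not depend on 172.

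**2. Inputs.**

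- Enrolled per arm: 1200/6 = 200. Equal allocation is implied by six groups in blocks of 12.
- Analysed per arm: the Statistics section excludes only patients who did not start treatment and carries the last observation forward, so about 200 is the fitting base. If the assumed 15% were lost, 200 × 0.85 = 170.
- Recovery on prednisolone alone: 80% (Patients and enrolment).
- Recovery on the combination: 80% as assumed in the plan. The values 85%, 88% and 90% are my assumptions, to show a range of real benefits; 90% adds the 10 points that the plan calls clinically significant against placebo.
- Endpoint: proportion completely recovered at 6 months, one combination arm against prednisolone alone.

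**3. Precision if both rates are 80%.** SE = √(2 × 0.8 × 0.2 / n).

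- n = 200: SE = √(0.32/200) = 0.0400; 95% half-width = 1.96 × 0.0400 = 7.8 points.
- n = 170: SE = √(0.32/170) = 0.0434; half-width = 8.5 points.

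**4. Chance of a non-significant result when the combination is truly better.** With p̄ the mean of the two rates, d their difference, SE₀ = √(2p̄(1 − p̄)/n) and SE₁ = √((p₁(1 − p₁) + p₂(1 − p₂))/n):

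P(non-significant) = 1 − Φ((d − 1.96·SE₀)/SE₁).

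For 80% vs 88% with n = 200: SE₀ = 0.0367, SE₁ = 0.0364, and (0.08 − 1.96 × 0.0367)/0.0364 ≈ 0.22, so the probability is 1 − Φ(0.22) ≈ 41%.

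| True rates | n = 200 | n = 170 |
|---|---|---|
| 80% vs 85% | 74% | 77% |
| 80% vs 88% | 41% | 48% |
| 80% vs 90% | 20% | 26% |

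If the rates are truly equal, a two-sided 5% test is non-significant about 95% of the time. P above 0.05 is therefore common both when the regimens are equal and when the combination is better by several points, and it cannot separate the two.

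**5. What a margin-based conclusion would have to meet.** The documents give no margin, so the margins m here are assumptions. With 80% in both arms and one-sided 0.025, power = Φ(m/SE − 1.96). At n = 200:

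- m = 5 points: Φ(1.25 − 1.96) = 24%
- m = 7.5 points: Φ(1.875 − 1.96) = 47%
- m = 10 points: Φ(2.5 − 1.96) = 71%

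None reaches 80%.

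**The case against.** The strongest reply is that the sentence is an indirect question in a forward-looking Discussion paragraph and is neither a hypothesis nor a decision rule. The aim elsewhere is superiority, the Discussion itself says staged acupuncture with corticosteroids may bring extra benefit, and tests of difference fit that aim. A significant result for the combination would answer the sentence with a no. The planned 95% intervals for the hazard ratio would show what size of effect remains open, and their interpretation may be set out in a full protocol or analysis plan that is not shown.

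Most of this stands. A reader might infer that the investigators will declare equal effectiveness whenever P exceeds 0.05. The document does not say so, and misreading is a risk only. A reader might also infer that non-significance is the expected outcome. That rests on one loosely worded sizing sentence, and the planned synergy test suggests the authors hope the combination does better, so plausible is the right word.

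The calculations have limits too. The Abstract names time to complete recovery as the primary outcome and Cox models are planned, so figures for a 6-month proportion illustrate scale and do not describe the hazard-ratio analysis.

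What the reply does not remove is the inconsistency in the current text. The promise of an as-effective determination has no matching hypothesis or margin, and an interval without a margin gives no rule for reaching that conclusion.

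**Conclusion.** The point holds as a mismatch between a promised conclusion and the stated aim and tests. It is not an error in the superiority analysis. With about 200 analysed per arm, a non-significant result would leave an interval of roughly ±7.8 points around the estimate (±8.5 with 170). It would occur about 41% (48%) of the time if the combination truly gave 88% against 80%, and about 20% (26%) of the time at 90% against 80%.

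These figures assume equal allocation, the plan's 80% on prednisolone alone, a single combination arm, a normal approximation, and the 6-month proportion as endpoint.

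A further tempting step is to take the plan's 10 points as a ready-made margin. The documents do not support it: 10 points is the whole assumed benefit of active treatment over placebo, so as a margin it could label prednisolone alone as effective while almost that much was being lost. Pooling the two combination arms to gain power would also merge the acute and resting stages that the trial sets out to distinguish.

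**What to change.** Reword the Discussion sentence to match the aim in the Abstract and Background, for example: *The results will show whether adding staged acupuncture to prednisolone improves recovery over prednisolone by itself.* Add to Statistics: *A non-significant result for this comparison will be treated as inconclusive and reported with its 95% confidence interval; it will not be taken as evidence of equal effectiveness.*

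If the sponsor wishes to keep an as-effective conclusion, it should justify in advance a margin for this add-on contrast, say how the interval will be read against it, and state the power. The 10-point difference from placebo should not be adopted by default.

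The rewording costs two sentences and no data. The price is that the protocol promises a narrower conclusion.
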